## Assignment of interventions: allocation

### Sequence generation {16a}

In this cluster-randomized trial, general practices throughout South Tyrol serve as the unit of randomization. After recruitment, these practices will be assigned to either the intervention or control group through a stratified randomization process. Stratification factors include the patients’ preferred language (Italian or German), the location of the practice (urban or rural), and the demographic characteristics of the general practitioners (sex and age). Sequences will be generated using computer software to pre-generate random assignments. Practices in the intervention group will use the ABCC tool via a provided tablet PC, while those in the control group will continue their usual care without access to the tool.

To maintain the integrity of this randomization process and control for potential confounding, these stratifying variables will be explicitly included in the analytical models.

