## Statistical methods

### Statistical methods for primary and secondary outcomes {20a}

The data evaluation process is based on the intention-to-treat principle. Initial analyses will be performed on the entire group of patients with COPD, asthma, type 2 diabetes, and heart failure, which also includes those with multiple conditions. Subsequently, the impact of the ABCC tool is examined separately for patients with COPD, asthma, type 2 diabetes, and heart failure, irrespective of the presence of coexisting conditions.

Considering the clustered design of the study, a three-level multilevel analysis will be conducted: general practice, patient, and measurement. The study will apply linear mixed models to analyze outcomes to account for the grouping of measurements within patients in general practice. Fixed factors will include “treatment group,” “time” (categorical), and “interaction between treatment group and time.”

Given that randomization of patients into the intervention or control groups is not feasible, factors believed or known to influence the perceived quality of care and/or the use of the ABCC tool will be regarded as potential confounders. The intervention or control group assignment hinges on the accessibility of the ABCC tool (i.e., the presence of the ABCC tool tablet PC in general practice). Potential confounders include ethnic background (native/Western foreigner/non-Western foreigners), multimorbidity (yes/no), educational status (low/middle/high), age (continuous in years), sex (male/female), body mass index (BMI, kg/m2, continuous), smoking habits (never/former/current), location of the general practice (urban/rural), year of the general practitioner’s graduation (less/more than 10 years ago), and general practice in a group setting (yes/no).

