Each potential confounder will be independently added to the aforementioned linear mixed model, and if it is significantly associated with the outcome (*p* ≤ 0.05), it will be considered a confounder. Both unadjusted and adjusted treatment effects will be reported along with their corresponding 95% confidence intervals and *p*-values. Statistical significance is set at *p* < 0.05. To account for multiple potential confounders, inverse probability of treatment weighting using propensity scores will be used as a sensitivity analysis. The use of hierarchical modeling aims to methodically evaluate the significance of confounders, prioritizing them by their theoretical relevance and observed impact on study outcomes. To ensure analytical robustness, R-squared values will further quantify each covariate’s contribution to the model.

The primary outcome will encompass all measurement times, including data collected at 6, 12, and 18 months. The analytic strategy will use longitudinal data collected at 6, 12, and 18 months, incorporating random effects models to account for the nesting of patients within practices. Model comparison techniques will be used to assess the fit of increasingly complex models to ensure that the analysis captures the impact of the intervention while accounting for provider variability within practices.

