### Methods for additional analyses (e.g., subgroup analyses) {20b}

In addition to the secondary objective of assessing the shift in perceived quality of care, employing the PACIC against regular care after 18 months, individually for each chronic condition, further subgroup analyses will be conducted based on age, sex, multimorbidity status, and educational level, as these factors could potentially influence perceived quality of care and the use of the ABCC tool.

Linear mixed models are used for these analyses, with the subgroups added as interaction terms to assess whether the effect of the intervention varied across different subgroups. The subgroup analyses are specified a priori in the study protocol to avoid data dredging.

Adjusted analyses will also be conducted to control for potential confounders. Factors known or hypothesized to be associated with perceived quality of care or the use of the ABCC tool will be considered potential confounders and adjusted for in the analysis, including national background, location of general practice, year of graduation of the general practitioner, and whether the general practice is part of a group.

For adjusted analyses, especially when significant confounders are identified, the Inverse Probability of Treatment Weighting method will be used as described by Hernán et al. [29]. This approach, designed to balance the distribution of observed baseline covariates across treatment groups, mitigates potential bias and is fundamental to estimating the causal effects of interventions.

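### Covariates for the adjusted treatment effect are chosen by their p-value against the outcome, which does not identify confounders and conflicts with the covariate rules in {16a} and {20b}

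*Protocol article*

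**What the plan says.** Section {20a} of the protocol article lists ten potential confounders: ethnic background, multimorbidity, education, age, sex, BMI, smoking, practice location, the GP's graduation year and group practice. The selection rule is: "Each potential confounder will be independently added to the aforementioned linear mixed model, and if it is significantly associated with the outcome". The threshold is p ≤ 0.05, and a candidate that passes is labelled a confounder. A hierarchical step then weighs the factors, "prioritizing them by their theoretical relevance and observed impact on study outcomes". On reporting: "Both unadjusted and adjusted treatment effects will be reported along with their corresponding 95% confidence intervals" and p-values. Neither effect is named as primary. Inverse probability of treatment weighting is a sensitivity analysis.

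The section introduces confounder control with "Given that randomization of patients into the intervention or control groups is not feasible" and adds: "The intervention or control group assignment hinges on the accessibility of the ABCC tool".

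Two other sections bear on the same model. Section {16a} states that "general practices throughout South Tyrol serve as the unit of randomization", with stratification by patients' language, practice location, and GP sex and age. It commits to putting these stratifying variables in the analytical models. Section {20b} says that factors thought to matter will be adjusted for, "including national background, location of general practice, year of graduation of the general practitioner, and whether the general practice is part of a group", with no p-value condition. It also makes weighting the method for adjusted analyses.

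**The concern.** A significant association with the outcome shows that a covariate is prognostic. It says nothing about whether the covariate differs between arms. With 36 practices, a non-significant result does not show that an imbalanced factor is harmless. The screen therefore does not test what its label claims.

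Because the set depends on the outcome data, it can differ between PACIC, EQ-5D-5L and PAM, and between the four condition subsets. The confidence intervals and p-values of the final model treat it as if it had been fixed in advance. With three inconsistent rules for what enters the model and no named primary estimate, two analysts who follow the article could report different adjusted effects.

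**Working it through.** **The three rules side by side**

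- {16a}: language, location, GP sex and GP age are always in the model.
- {20a}: location enters only if p ≤ 0.05. Language, GP sex and GP age are not candidates; GP graduation year is.
- {20b}: national background, location, graduation year and group practice are adjusted for unconditionally. All four also appear in {20a} and the list is open-ended, so the conflict lies in the condition, not in the membership.

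**Inputs from {14}**

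Difference 0.49, SD 0.96 (0.51 SD), two-sided 0.05, power 90%, ICC 0.05, 10 patients per practice, 25% dropout, 36 practices. The plan's own size reproduces: the exact t-test gives 82 per group, and 82 × 1.45 / 0.9 / 0.75 = 176.1, rounded up to 177. Analysed patients per practice: 10 × 0.75 = 7.5, so 36 × 7.5 = 270 in all.

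**Chance that the screen keeps a real binary factor** (single 18-month endpoint, noncentral t). Effect sizes and prevalences are assumptions, since the document gives none.

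- Practice level: variance of a practice mean = 0.05 + 0.95/7.5 = 0.177. SE = √(0.177 / (36·p·(1−p))), which is 0.140 at p = 0.5 and 0.153 at p = 0.3. With 33 df, a 0.25 SD factor is kept in 41% and 36% of trials.
- Patient level: SE = √(0.95 / (270·p·(1−p))), which is 0.119 at p = 0.5 and 0.148 at p = 0.2. A 0.20 SD factor is kept in 39% and 27%.
- Stronger factors (p = 0.3 to 0.5): patient level at 0.3 SD, 64–71% kept; practice level at 0.4 SD, 72–79% kept.

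**False inclusion.** If all ten candidates were null and independent, the chance of keeping at least one is 1 − 0.95¹⁰ = 40%.

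**Effect on the test.** Simulated trials of 36 practice means (18 against 18) with no treatment effect: each of three binary practice-level factors is screened alone next to arm, then the model is refitted with those kept. The comparison is the model with all three.

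| Three factors | Type I error, screened | Type I error, fixed | SD of estimate, screened | SD of estimate, fixed |
|---|---|---|---|---|
| 0.3 SD each | about 6.5% | about 5.1% | 0.158 | 0.147 |
| pure noise | about 5.6% | about 4.9% | 0.141 | 0.146 |

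**Stability.** A second simulation had 3,000 trials of 36 practices × 8 patients and ten candidates, five of them real at 0.2 SD. It produced 237 different covariate sets, the most common in 10% of trials. On average 1.7 of the 5 real factors were kept, and at least one was dropped in 99% of trials. The SD of the difference between the screened and the full-set estimate was 0.05 SD, about a tenth of the planned effect (0.05/0.51 = 0.098).

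**The case against.** Several points on the other side stand.

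- **Large bias.** A reader might infer that dropping a 0.25 SD factor with a 40-point imbalance biases the effect by 0.25 × 0.40 = 0.10 SD, 20% of the planned 0.51 SD. The documents do not support this as an expected harm. With 18 against 18 practices, a gap of 7/18 (39 points) or more arises in only about 2–3% of unstratified allocations at prevalence 0.3–0.5, and location is stratified. If baseline is a level of time in the mixed model, a time-constant covariate added as a main effect also largely cancels from the group-by-time contrast. In a check with complete data the contrast did not move, and with 25% dropout it moved by at most 0.005 SD. {20a} names only 6, 12 and 18 months, so that reading is not certain. Under it, the simulated differences above, which use one value per practice, would shrink too.
- **No randomisation.** A reader might infer that the plan treats the trial as unrandomised. The clause about patients is true of a cluster trial. Only the sentence on tool accessibility misleads, because the tablet follows the randomised allocation. Unblinded practices recruit patients after allocation, so patient-level imbalance is possible and adjustment is reasonable.
- **Different sets by visit.** One longitudinal model is fitted, so its covariate set does not change between visits.
- **Other estimates.** The unadjusted effect is untouched by the screen and is reported, as is the weighted sensitivity analysis. {16a} already supplies a fixed core of covariates.

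None of this defends the selection rule or resolves the conflict between the three sections.

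**Conclusion.** The concern holds as a fault in how covariates are chosen and in the consistency of the plan. The screen does not identify confounders, makes the adjusted model depend on the outcome data, and contradicts {16a} and {20b}. Its cost is modest: type I error about 6.5% instead of about 5%, and an SD of the estimate about 7% larger (0.158/0.147 = 1.07), when three practice-level factors of 0.3 SD are real. These figures rest on ICC 0.05, 36 practices, 7.5 analysed patients each, a single-endpoint analysis, and effect sizes that the document does not give. Strong factors would mostly be kept. Neither a large bias nor a serious inflation of the error rate is shown. The unnamed primary estimate adds to the problem, because the unadjusted effect protects the conclusion only if it is declared primary.

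**What to change.** - Delete the p ≤ 0.05 rule and the criterion of observed impact in {20a}.
- Name one fixed covariate set before any outcome data are seen: the {16a} stratification factors plus a short prognostic list, for example age, sex, multimorbidity and education. Use it for every outcome and condition subset, whatever the p-values.
- Align {20a} and {20b} with {16a}, including the role of weighting.
- State which of the unadjusted and adjusted effects is primary.
- Reword the sentence on tool accessibility to say that group is the randomised allocation of the practice, and justify adjustment by precision and by patient recruitment after unblinded allocation.

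The cost is wording and a few degrees of freedom, with slightly lower precision if the chosen covariates prove not to be prognostic (SD 0.146 against 0.141 in the noise case). The sample size is unchanged. The trial status section reports that recruitment has not begun, so the change can be made before outcome data exist.

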**Methods:**

This is a cluster-randomized study involving approximately 400 patients with COPD, asthma, type 2 diabetes, and heart failure who received care from the South Tyrolean General Practices. Initially, the ABCC tool will be translated into German and Italian and validated. Subsequently, half of the participants will use the validated ABCC tool for patient-reported outcome measurement assessments, while the other half will receive usual care. The primary outcome measure is the change in the patients’ perception of the quality of care after 18 months. The secondary outcomes included changes in quality of life, self-management behavior, and healthcare utilization. The missing data will be managed using multiple imputations. Additionally, a cost-effectiveness analysis that considers the direct medical costs reimbursed by the National Health Service will be conducted.

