### Criteria for discontinuing or modifying allocated interventions {11b}

Given that the ABCC tool is used and then the participant is followed up with measurements for up to 1 year, the criteria for discontinuation of the intervention itself are as follows: (i) participants have the right to withdraw their consent at any time, for any reason. If a participant wishes to discontinue the use of the ABCC tool after it has been administered but before the follow-up period, their request should be honored. (ii) If a participant experiences significant emotional distress during the initial administration of the ABCC tool that cannot be adequately addressed, intervention discontinuation is warranted. (iii) If a participant’s health status changes significantly immediately after using the ABCC tool such that the tool is no longer appropriate or relevant, discontinuation of the intervention might be necessary. (iv) If a technical error occurred during the initial administration of the ABCC tool that rendered the results invalid or unusable and it is not feasible to re-administer the tool, discontinuation of the intervention might be the best course of action.

In cases where discontinuation of the ABCC tool intervention is being considered, the decision will be made through a collaborative process involving the participant and their GP. The coordinating center is available to provide guidance and support in this decision-making process, ensuring compliance with study protocols and ethical standards.

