### Outcomes {12}

#### Primary outcome

The primary objective of this study is to assess changes in perceived quality of care over an 18-month period using the Patient Assessment of Chronic Illness Care (PACIC) [20, 21] as the comparative measure. This assessment will be administered at baseline and then at specified follow-up points to determine changes from usual care in the cohort of participants.

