#### Secondary outcomes

Secondary objectives encompass several areas:

Assessing the shift in perceived quality of care, employing the PACIC, against regular care after 18 months, individually for each chronic condition.We evaluate variations in perceived quality of care, gauged by the PACIC, against regular care at 6- and 12-month intervals for both the entire participant group and each chronic condition individually.Evaluate changes in universal health-related quality of life, as gauged by the EQ-5D-5L [21, 22], in comparison with standard care at 6-, 12-, and 18-month intervals for the entire participant group and for each chronic condition separately.Scrutinizing changes in participant activation, as measured by the Patient Activation Measure (PAM) [23, 24], against standard care at 6-, 12-, and 18-month intervals for both the entire participant group and for each chronic condition.Conducting practice-level analyses to evaluate the overall impact of the ABCC tool on healthcare delivery and outcomes. This includes assessing changes in practice-wide metrics for average improvements in PACIC scores, EQ-5D-5L outcomes, and PAM levels, comparing the aggregated results of the intervention group practices against those of the control group practices.

In addition, we will assess the cost-effectiveness of the ABCC tool compared with usual care after an 18-month period. This analysis focuses on the direct medical costs reimbursed by the National Health Service (NHS). The economic resources claimed will be obtained from the data of general practitioners, the health administration of the province, and the South Tyrolean ambulance service. Only costs and benefits from the healthcare perspective are considered and will include the following:

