#### End of study

The study will conclude after the 18-month follow-up assessment, at which point the primary and secondary outcomes will be evaluated. The primary outcome will be the perceived quality of care as measured by PACIC for the entire participant group and for each chronic condition separately. Changes in quality of life (EQ-5D-5L) and patient activation (PAM) at different time points led to secondary outcomes.

The expected duration of the entire study, including the enrollment, intervention, evaluation, and close-out phases, is expected to be two and a half years. This timeframe includes the pre-allocation preparation phase, the 18-month period for implementation of interventions and conduct of assessments, and additional months for initial recruitment and final analysis.

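### The protocol defines the primary outcome in conflicting ways (18 months or all visits; whole group or also each condition), while the sample size supports one whole-group comparison

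*Protocol article*

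**What the plan says.** **Time point.** The abstract (Methods) states: "The primary outcome measure is the change in the patients’ perception of the quality of care after 18 months". The key question in Objectives {7} is also set at 18 months. The Primary outcome section is looser; its aim is to "assess changes in perceived quality of care over an 18-month period using the Patient Assessment of Chronic Illness Care (PACIC"), and it does not name the follow-up points. The Secondary outcomes section lists PACIC "against regular care at 6- and 12-month intervals for both the entire participant group and each chronic condition individually". Statistical methods {20a} states: "The primary outcome will encompass all measurement times, including data collected at 6, 12, and 18 months".

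**Population.** End of study states: "The primary outcome will be the perceived quality of care as measured by PACIC for the entire participant group and for each chronic condition separately". The Secondary outcomes section lists the 18-month PACIC comparison within each condition as secondary. Section {20b} agrees, opening with "In addition to the secondary objective of assessing the shift in perceived quality of care, employing the PACIC against regular care after 18 months" and applying it to each condition. Section {20a} analyses the whole group first and the conditions afterwards.

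**Size and error rate.** Sample size {14} rests on one independent-samples t-test at two-sided 5% with 90% power and names neither a visit nor a population. Section {20a} sets significance at p < 0.05. The article gives no rule for several primary tests.

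**Length of follow-up.** Section {11b} says that "the participant is followed up with measurements for up to 1 year", whereas Table 2 and the section on follow-up assessments run to 18 months.

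**The concern.** The same results are called primary in one place and secondary in another. PACIC at 6 and 12 months is secondary in the outcome list and part of the primary outcome in {20a}. PACIC within each condition is secondary in the outcome list and in {20b}, and primary in End of study. An analysis plan written under this protocol could cite it for any of these versions.

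Two things are at stake. The 5% level and the 90% power belong to one comparison, and do not carry over if several visits or several conditions are primary. Also, the possible answers over time (month 18, the average over visits, a joint test of all visits) are different hypotheses with different power, so the choice can change the trial's conclusion. It should be fixed before data are seen.

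**Working it through.** **1. The plan's own figure.** Inputs from Sample size {14}: difference 0.49, SD 0.96, d = 0.49/0.96 = 0.51, two-sided α = 0.05, power 90%, ICC 0.05, 10 patients per practice, cluster-size factor 0.9, dropout 25%.
- Two-sample t-test: 81.8, rounded up to 82 per group.
- Design effect: 1 + (10 − 1) × 0.05 = 1.45.
- 82 × 1.45 / 0.9 / 0.75 = 176.1, rounded up to 177.

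The figure reproduces. With 180 per group the effective number is 180 × 0.75 × 0.9 / 1.45 = 83.8, and power for one comparison is about 91% (normal approximation: Φ(0.51/√(2/83.8) − 1.96)).

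**2. False-positive risk if any one test could count as success.** This rule is an assumption. The figures are simulated from correlated normal test statistics, each tested at |z| > 1.96.

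| Set of primary tests | Assumption | Chance of at least one false positive |
|---|---|---|
| Whole group, 3 visits | correlation 0.4 | 13.1% |
| Whole group, 3 visits | correlation 0.7 | 10.9% |
| Whole group, 3 visits | correlation 0.9 | 8.3% |
| Whole group + 4 conditions, one visit | four equal disjoint groups | 20.4% |
| Whole group + 4 conditions, one visit | every patient has exactly two conditions, all pairs equally common | 17.7% |

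**3. Power within one condition.** The protocol gives no expected number per condition. Two cases: an equal split without overlap, 180/4 = 45 recruited per arm; and every patient having two conditions, 90 per arm. Effective n = recruited × 0.75 × (0.9 or 1) / design effect; power = Φ(0.51/√(2/n) − 1.96).

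| Recruited per arm | Design effect | Cluster-size factor | Effective n | Power |
|---|---|---|---|---|
| 45 | 1.45 (the plan's) | 0.9 | 20.9 | 38% |
| 45 | 1.075 (45/18 = 2.5 per practice) | 0.9 | 28.3 | 48% |
| 45 | 1.044 (1.875 per practice after dropout) | 1 | 32.3 | 54% |
| 90 | 1.45 (the plan's) | 0.9 | 41.9 | 65% |
| 90 | 1.2 (90/18 = 5 per practice) | 0.9 | 50.6 | 73% |
| 90 | 1.1375 (3.75 per practice after dropout) | 1 | 59.3 | 79% |

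Every case is below 90%.

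**4. Does the time contrast matter?** Assumed between-visit correlation 0.5, effective n 83.8 per group.

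| Assumed effect at 6, 12, 18 months | Month 18 | Average over visits | Joint 3-df test |
|---|---|---|---|
| 0.17, 0.34, 0.51 | 91% | 77% | 84% |
| 0.51, 0.51, 0.51 | 91% | 98% | 94% |

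The three tests can differ clearly, in either direction, depending on how the effect develops.

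**The case against.** The strongest reply is that most of the text points one way. The abstract, the key question and the secondary list favour 18 months; the secondary list, the order of analysis in {20a} and section {20b} favour the whole group. The sentence in {20a} can be read as saying which data enter the mixed model, since the next sentence describes a longitudinal strategy. The Primary outcome section, with its change over an 18-month period, is compatible with that. The choice among model contrasts is commonly left to a statistical analysis plan, which is not shown.

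Much of this stands. The Primary outcome section does not by itself fix month 18, and an unnamed contrast alone would be no finding. But the sentence in {20a} speaks of the primary outcome, not of model inputs. Even on the charitable reading, End of study still contradicts the secondary list and {20b} on the conditions.

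A reader might go further and infer that the trial may claim success on any of 3 visits × 5 populations, 15 tests. The documents do not support that. End of study adds conditions at the close of the 18-month follow-up, {20a} adds visits for the primary outcome without mentioning conditions, and per-condition PACIC at 6 or 12 months is nowhere called primary. Nor is there any rule that one significant test suffices.

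A reader might also treat the conditions as separate groups. Section {20a} analyses each condition regardless of coexisting ones, so the groups overlap and the disjoint figures are one extreme.

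**Conclusion.** The protocol contradicts itself on what is primary, in time and in population. That conclusion rests on the current text alone and needs no numerical assumption. The sample-size arithmetic is right, but it supports one whole-group comparison.

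The sizes are conditional. The error rates of about 8–13% (three visits) and 18–20% (whole group plus four conditions) hold only if any single unadjusted test could be claimed as success, and they depend on the assumed correlation and overlap. The power of about 38–54% or 65–79% per condition depends on the assumed group sizes and design effect, with d = 0.51, ICC 0.05 and 25% dropout. What holds across these cases is that the stated 90% is not delivered for the single conditions. One joint or average test over visits would keep the 5% level, but it would answer a different question from the 18-month one.

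The one-year follow-up in {11b} is a separate inconsistency. It does not define the primary outcome.

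**What to change.** 1. Name one primary contrast: the between-arm difference in PACIC at month 18 in the whole randomised population, estimated from the mixed model and tested at two-sided 5%. Most of the protocol already favours this.
2. Reword the sentence in {20a} so that the 6- and 12-month data enter the model as supporting data and their results are reported as secondary.
3. In End of study, delete the words that extend the primary outcome to the separate conditions.
4. State in Sample size {14} that the calculation refers to this contrast.
5. Separately, reconcile the follow-up length in {11b} with Table 2 and the section on follow-up assessments.

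This costs wording only. The sample size is unchanged, and Trial status says that recruitment had not begun. Keeping several primary tests would cost patients: with a Bonferroni correction and 90% power for each whole-group test, three visits need 106 × 1.45 / 0.9 / 0.75, rounded up to 228 per group, and the whole group plus four conditions needs 117 × 1.45 / 0.9 / 0.75, rounded up to 252. The latter would still not give 90% power within a condition.

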### Sample size {14}

The sample size estimation was guided by analogous assumptions from a concurrent study conducted in the Netherlands, thereby offering a relevant frame of reference for our calculations. The study’s primary outcome will be determined through the Patient Assessment of Chronic Illness Care (PACIC) measure. Given the lack of substantial data on the minimum significant difference and standard deviation for the PACIC in this specific population, an estimated medium effect size of 0.51 is derived from the work of Slok et al. [26]. This is based on an observed mean difference of 0.49 between the intervention and control groups, and a pooled within-group standard deviation of 0.96 from the same study.

For the current study, using an independent samples *t*-test, a significance level of 0.05 for two-sided testing, a power of 90%, and an even split between intervention and control groups, it is estimated that each group should include 82 patients. However, as patients will be grouped within general practices, this number is adjusted to account for the design effect, which is calculated as 1 + (m − 1) × ICC (intraclass correlation), where an ICC of 0.05 and an average of 10 patients per general practice is assumed [6].

After adjusting for cluster design (multiplication factor of 1.45), variable cluster sizes (division by 0.9), and an anticipated dropout rate of 25% (division by 0.75), it was estimated that each group would require 177 participants. Each group will need to include 18 general practices with an average of 10 patients per general practice. Therefore, 360 participants (180 per group) from 36 general practices (18 per group) will be recruited for this cluster-randomized study.

The aim was to achieve a balanced distribution among the various chronic conditions. However, given that healthcare providers are not explicitly instructed to strive to achieve this balance, this may not be ensured.

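### Baseline PACIC is collected from every participant but is missing from the primary model and the confounder list, and the text does not settle whether month 0 is a level of time

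*Protocol article*

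**What the plan says.** Under Primary outcome, the target is change in PACIC over 18 months, and of the instrument the article says: "This assessment will be administered at baseline and then at specified follow-up points". The SPIRIT schedule (Table 2) and the enrolment section confirm a baseline PACIC, EQ-5D-5L and PAM for everyone enrolled.

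Statistical methods {20a} sets out a three-level linear mixed model (practice, patient, measurement). Its named fixed factors are treatment group, categorical time and the "interaction between treatment group and time". Ten potential confounders follow, from ethnic background to group practice, each to be kept if its p-value is 0.05 or less. Baseline PACIC is not one of them, and it is not in the shorter adjustment list under additional analyses {20b}.

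On the data used, {20a} says "The analytic strategy will use longitudinal data collected at 6, 12, and 18 months". The sentence just before it says that the primary outcome covers all measurement times and then names the same three visits. Month 0 is neither clearly in nor clearly out.

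**The concern.** The baseline value of an outcome is usually among its strongest predictors. Here it is collected at no extra cost, yet it has no stated role as a covariate, while BMI and smoking are screened for one.

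The two readings of the time factor give different estimators. With months 6, 12 and 18 only, the month-18 contrast ignores baseline, and a chance baseline difference between arms feeds through in part. With month 0 as a further level and arm means left free, the month-18 interaction is a difference in change. That subtracts the whole baseline difference, although part of a chance difference would have faded by regression to the mean.

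Imbalance is a realistic prospect. There are 36 practices, patients are enrolled after their practice has been allocated, and the recruiting providers know the allocation.

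**Working it through.** **Inputs.** From Sample size {14}: "observed mean difference of 0.49 between the intervention and control groups"; "a pooled within-group standard deviation of 0.96 from the same study"; 5% two-sided, 90% power, ICC 0.05, 10 patients per practice, factor 0.9 for variable cluster size, 25% dropout, 18 practices and 180 patients per group. Assumed, because the document gives no figure: correlation r between baseline and month-18 PACIC of 0.3, 0.5 or 0.7. Also assumed: a practice effect that is stable over time, as a simple practice intercept implies.

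**The plan's own figure.** The t-test needs 81.6, so 82 per group. Then 82 × 1.45 / 0.9 / 0.75 = 176.1, so 177. Both stated numbers reproduce, and neither takes credit for baseline.

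**Power as planned, follow-up only.** Effective n per group = 180 × 0.75 × 0.9 / 1.45 = 83.8. SE = 0.96 × √(2/83.8) = 0.148. Power is 91% by the normal approximation, or 89% with 34 degrees of freedom for 36 practices.

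**Month-18 standard errors under three models.** Take 18 practices per arm with 8 completers each (7.5 rounded up). Write c = 2 × 0.96² / 18 = 0.1024.

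1. *Months 6, 12 and 18 only.* Variance = c × [0.05 + 0.95/8] = 0.1024 × 0.16875 = 0.01728. SE 0.131 at any r.
2. *Month 0 as an unconstrained level.* The practice and patient intercepts cancel, so variance = c × 2(1 − r)/8 = 0.01792 / 0.01280 / 0.00768. SE 0.134 / 0.113 / 0.088.
3. *Baseline-adjusted, common baseline mean.* The correlation between baseline and month-18 arm means is λ = [0.05 + (r − 0.05)/8] / 0.16875 = 0.481 / 0.630 / 0.778. Variance = 0.01728 × (1 − λ²) = 0.01327 / 0.01043 / 0.00683. SE 0.115 / 0.102 / 0.083.

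A patient-level baseline covariate does almost as well. With the within-practice slope b = (r − 0.05)/0.95, variance = c × {0.05(1 − b)² + [0.95(1 + b²) − 2b(r − 0.05)]/8}, giving SE 0.119 / 0.104 / 0.084 before the small cost of estimating b.

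| Assumed r | Follow-up only | Unconstrained change | Common baseline mean | Baseline covariate |
|---|---|---|---|---|
| 0.3 | 0.131 | 0.134 | 0.115 | 0.119 |
| 0.5 | 0.131 | 0.113 | 0.102 | 0.104 |
| 0.7 | 0.131 | 0.088 | 0.083 | 0.084 |

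These standard errors leave out the 0.9 factor and round completers up, so they sit below the 0.148 above. They are for comparing models, not for restating power.

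**Size of a chance imbalance.** With 180 per arm, SE of the baseline difference = 0.96 × √(2 / (180 × 0.9 / 1.45)) = 0.96 × √(2/111.7) = 0.128. The 95% range is about ±0.25 points, against a planned effect of 0.49. Ignoring the shared practice effect, a follow-up-only contrast is expected to carry r times the baseline difference, and a change contrast −(1 − r) times it. With the stable practice effect, λ takes the place of r.

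**The case against.** The lists are not worded as closed: both the fixed factors and the confounders are introduced as inclusions. The sequence-generation section also promises that the stratification variables will be in the models, yet language and the practitioner's sex and age are in neither list. Absence from {20a} is therefore not exclusion, and an analysis plan that is not shown could add baseline. That stands as a caution, but it does not dispose of the point. The article goes as far as naming the model terms, the candidate covariates, a selection rule and the visits, and a plan that followed it would leave baseline PACIC out.

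A reader might infer that the month-18 comparison is bound to retain baseline imbalance. The documents do not support that. The definition of the outcome as change, and the reference to all measurement times, allow month 0 to be a time level, in which case the baseline difference is subtracted.

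A reader might also infer that a change analysis would cost much power at low correlation, since the textbook variance factor 2(1 − r) is 1.40 at r = 0.3 and passes 1 at r = 0.5. That does not carry over to this model. A stable practice intercept cancels from change, so the ratio to follow-up-only is 0.01792 / 0.01728 = 1.04 at r = 0.3. The crossover is at r = 1 − 1.35/2 = 0.325, where 1.35 = 1 + 7 × 0.05 is the design effect for 8 completers.

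**Conclusion.** The point holds as an avoidable loss of precision together with an ambiguity that needs settling. Under either reading of the time factor, the stated model is less precise than one that adjusts for baseline PACIC, at every correlation examined. Using the common-baseline-mean figures, adjustment leaves 77% / 60% / 40% of the follow-up-only variance and 74% / 81% / 89% of the change variance at r = 0.3 / 0.5 / 0.7.

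It would be wrong to conclude that the trial is underpowered: follow-up-only power is 89% to 91% against a planned 90%. The size of the gain rests on a correlation that the document does not give, and on a practice effect that is constant over time. The statements about carry-over and over-correction concern chance imbalance. For systematic differences produced by unblinded recruitment after allocation, neither a change contrast nor covariate adjustment is sure to be unbiased.

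**What to change.** State in {20a} whether month 0 is part of the response. Pre-specify baseline PACIC, with a baseline by time term, as a fixed covariate in the primary model for months 6, 12 and 18, kept whatever the p ≤ 0.05 confounder screen shows. Do the same with baseline EQ-5D-5L and baseline PAM for those outcomes.

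The covariate form is preferable here to constraining the arm means to be equal at baseline. That constraint presumes equal expected baselines, and enrolling patients unblinded after practice allocation puts this in doubt. Adjustment reduces any resulting selection bias but does not remove it, and the write-up should say so.

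The cost is a sentence or two in the protocol and the analysis plan. The measurements are already scheduled, and the trial-status section says that recruitment has not begun.
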